## Abstract

**Background:**

Approximately 1 in 5 patients feel unsatisfied after total knee arthroplasty (TKA). Prognostic tools may aid in the patient selection process and reduce the proportion of patients who experience unsatisfactory surgery. This study uses the prognostic tool *SMART Choice (Patient Prognostic Tool for Total Knee Arthroplasty)* to predict patient improvement after TKA. The tool aims to be used by the patient without clinician input and does not require clinical data such as X-ray findings or blood results. The objective of this study is to evaluate the *SMART Choice* tool on patient decision making, particularly willingness for surgery. We hypothesise that the use of the *SMART Choice* tool will influence willingness to undergo surgery, especially when used earlier in the patient TKA journey.

**Methods:**

This is a multicentred, pragmatic, randomised controlled trial conducted in Melbourne, Australia. Participants will be recruited from the St. Vincent’s Hospital, Melbourne (SVHM) Orthopaedic Clinic, and the client base of HCF, Australia (private health insurance company). Patients over 45 years of age who have been diagnosed with knee osteoarthritis and considering TKA are eligible for participation. Participants will be randomised to either use the *SMART Choice* tool or treatment as usual. The *SMART Choice* tool provides users with a prediction for improvement or deterioration / no change after surgery based on utility score change calculated from the Veterans-RAND 12 (VR-12) survey. The primary outcome of the study is patient willingness for TKA surgery. The secondary outcomes include evaluating the optimal timing for tool use and using decision quality questionnaires to understand the patient experience when using the tool. Participants will be followed up for 6 months from the time of recruitment.

**Discussion:**

The *SMART Choice* tool has the potential to improve patient decision making for TKA. Although many prognostic tools have been developed for other areas of surgery, most are confined within academic bodies of work. This study will be one of the first to evaluate the impact of a prognostic tool on patient decision making using a prospective clinical trial, an important step in transitioning the tool for use in clinical practice.

**Trial registration:**

Australia and New Zealand Clinical Trials Registry (ANZCTR) - ACTRN12622000072718. Prospectively registered – 21 January 2022.

## Background

Knee osteoarthritis (OA) is a progressive and debilitating condition for sufferers. Pain and stiffness are common presenting complaints. Without adequate intervention, functional decline and even complete loss of independence can occur [1]. Lifestyle modification, analgesia and physiotherapy comprise the core of nonoperative management [2]. In certain situations, intra-articular injections may delay the need for surgery [3, 4]. Failing nonoperative management, the definitive treatment option for knee OA is total knee arthroplasty (TKA) [5].

Based on registry studies, TKA is generally regarded as a successful procedure [6, 7]. The risk of adverse events associated with surgery is relatively low, and the probability of improving symptoms is relatively high [8, 9]. However, recent studies have reported that up to 20% of patients remain unsatisfied after TKA [10, 11]. For these patients, ongoing symptoms from TKA severely impact their quality of life [12, 13]. With a current trend towards more arthroplasty surgeries globally, the social and economic impact of TKA dissatisfaction is a fast-growing problem [14].

To address this issue, solutions need to arise from multiple fronts. Improvements in surgical techniques and implant design seem to be the most obvious path forward. However, substantial progress has already been made from pioneers of the past. The trajectory of progress from technique and implant design alone is reaching a plateau [15, 16]. Furthermore, patients are dissatisfied despite what surgeons would perceive as successful surgery [17]. An alternative solution to TKA would be a completely new treatment for knee OA; a solution that addresses both the symptoms and natural history of the disease. Work is underway to experiment with biologic agents aimed at regenerating cartilage and bone [18–21]. However, this process is expensive and time consuming without any guarantee of success. Research must therefore explore complementary pathways to find solutions for TKA dissatisfaction.

One of these pathways is through improvement of patient-specific factors. The goal here is to optimise patients to become excellent surgical candidates. Prognostic tools fit into this area of research. These are tools developed to predict surgical outcomes. This is clinically useful in two ways. First, if poor outcomes can be predicted before surgery, then patients can be stratified into groups based on risk. For high-risk patients, resources can be set aside to improve modifiable risk factors. This may optimise the patients for surgery. Second, prognostic tools can manage patient expectations through informed decision making. A patient who understands their potential outcomes may regress their expectations towards what is realistic for their circumstances. This is based on the understanding that a major driver of dissatisfaction is the imbalance between expected and actual outcomes [22, 23]. The premise is that prognostic tools can better align these two perceptions to improve patient satisfaction and positively influence patient decision making around surgery.

The *SMART Choice* tool is a patient-focused prognostic tool that predicts clinical outcomes after TKA. The term “patient focused” means that a patient can use the tool without the input of a clinician. This allows the tool to be used early in the patient TKA journey. The *SMART Choice* tool was developed using data from the St. Vincent’s Melbourne Arthroplasty Outcomes (SMART) Registry– an extensive arthroplasty registry with over 14,000 patients and more than 20 years of follow-up time [24]. From this data, the *SMART Choice* tool can predict the chance of success. The tool defines success as an improvement in the health-related quality of life (HRQoL) utility score based on the previously calculated minimal clinically important difference (MCID) [25]. With the use of this tool, patients can gain benefits through two pathways: 1) informed decision making for the patient, and 2) managing patient expectations in preparation for TKA.

The rationale for this study is to evaluate the *SMART Choice* tool in a pragmatic clinical environment. We aim to investigate the influence of the *SMART Choice* tool on patient decision making and the optimal timepoint to use this tool in the patient TKA journey. Willingness for surgery is used as a proxy measurement for patient decision making because waiting for true occurrences of TKA would be unfeasible.

## Methods

This protocol is published in accordance with the SPIRIT (Standard Protocol Items for Randomised Trials) guidelines [26]. Furthermore, the *SMART Choice* tool was developed in accordance with TRIPOD (Transparent Reporting of Multivariable Prediction Model for Individual Prognosis or Diagnosis) Statement guidelines [27].

### SMART Choice tool development

This tool is being developed using a combination of traditional statistical methods and machine learning algorithms. Three thousand seven hundred fifty-five patients who underwent primary TKA procedures recorded on the SMART Registry between 2006 and 2019 will be analysed. Logistic regression, classification tree, XG boosted tree, and random forest models will be developed using sample splitting, 10-fold cross validation and bootstrapping techniques. Predictors considered include age at surgery, gender, and Veterans-RAND 12 (VR-12) responses. The model will predict a probability score (0–1) for improvement after TKA. From the probability score, participants will be stratified into deciles where the actual outcomes are reported as the output for the *SMART Choice* tool (Table 1).

**Table 1 Tab1:** An example of probability score output from the *SMART Choice* tool development which correlates with a predicted outcome and actual outcome. The actual outcome within each decile will be reported to participants who use the tool. *Final probability scores will be determined once the SMART Choice tool predictive model is finalised *

Decile	Probability for Improvement (mean; range)	Predicted Outcome (n)	Actual Outcome (n; %)	
			Improvement	Deterioration/No Change
**1**	0.315 (0.119–0.402)	Deterioration/No Change (69)	24 (34.8)	45 (65.2)
**2**	0.456 (0.406–0.499)	Deterioration/No Change (69)	29 (42.0)	40 (58.0)
**3**	0.535 (0.501–0.564)	Deterioration/No Change (69)	29 (42.0)	40 (58.0)
**4**	0.586 (0.565–0.610)	Deterioration/No Change (69)	37 (53.6)	32 (46.4)
**5**	0.632 (0.610–0.651)	Deterioration/No Change (5)	1 (20.0)	4 (80.0)
		Improvement (63)	44 (69.8)	19 (30.2)
**6**	0.669 (0.652–0.688)	Improvement (68)	43 (63.2)	25 (36.8)
**7**	0.704 (0.688–0.725)	Improvement (68)	50 (73.5)	18 (26.5)
**8**	0.742 (0.726–0.764)	Improvement (68)	54 (79.4)	14 (20.6)
**9**	0.788 (0.764–0.812)	Improvement (68)	57 (83.8)	11 (16.2)
**10**	0.845 (0.812–0.928)	Improvement (68)	60 (88.2)	8 (11.8)

### Study design and setting

This is a prospective, pragmatic, assessor-blinded, superiority randomised controlled trial evaluating participants who have been diagnosed with knee OA and are considering TKA. Participants will be recruited from two sources: St. Vincent’s Hospital Melbourne (SVHM) Orthopaedic Outpatient Clinic and HCF (private health insurance company) client base across Australia.

From the SVHM source, patients who have been referred to an orthopaedic surgeon for consideration for TKA will be targeted for recruitment. This information can be found on clinic appointment lists in advance of 3 months. Patients who are referred to the clinic often wait up to 1 year to be seen by an orthopaedic surgeon. Following consultation, if deemed appropriate for surgery, patients may wait for another 6–12 months before the surgery is performed. Often, patients who are seen at SVHM are already in the later stages of the TKA journey as a product of resource constraints and waiting lists at the hospital.

In comparison, patients from the HCF source are at various stages of the TKA journey. As expected, some patients may be very early in disease progression, with symptoms being adequately managed by their general practitioner (GP). However, other patients may be more advanced in their disease progression and may have already made an application for TKA funding. Potential participants here will be recruited from internal advertising.

Having a diverse recruitment pool with patients at all stages of the TKA journey can help us evaluate the optimal timepoint for *SMART Choice* tool usage. We hypothesise that patients earlier in the TKA journey may be more open to decision making with consideration of predicted outcomes. In contrast, patients who are further along the TKA journey may feel too invested for the tool to influence decision making around willingness for surgery. The optimal timepoint for *SMART Choice* tool usage will be evaluated from a sub analysis of patients at different timepoints in the TKA journey.

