### Randomisation, allocation, and blinding

Participants will be randomly allocated in a 1:1 ratio into two groups: intervention and treatment as usual (TAU). Allocation will be performed using a computer-generated simple randomisation schedule of consecutive patients. The randomisation will be embedded into the web-based platform that hosts the study portal. All participants who meet the eligibility criteria will be randomised.

Due to the nature of the study, participants will remain unblinded from their allocation group. However, limited disclosure of allocation groups will be applied to prevent participants who are allocated to TAU from proactively seeking out online prognostic tools to use. Investigators (excluding research assistants who will not be involved in data analysis) will remain blinded to the allocation group and identity of patients until after final data analysis is performed. Surgeons will be blinded to the allocation group of their patients and will have no influence on the outcome of allocation or intervention.

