**Fig. 2 Fig2:**
[figure not shown]
Flow diagram describing the study procedure. SVHM: St. Vincent’s Hospital, Melbourne; HCF: Hospitals Contribution Fund Australia; VR-12: Veterans RAND-12; EQ-5D-3L: EuroQol 5 Dimensions 3 Levels; TAU: treatment as usual; K-DQI: Knee Decision Quality Instrument; SURE: decisional conflict screening tool

All recruited participants will be asked to complete a baseline questionnaire within the study portal. This provides an understanding of the participant’s general characteristics. The questionnaire will capture contact details, date of birth, sex, height, weight, comorbidities, medications (analgesia), smoking status, time with knee OA symptoms (years), previous nonoperative management of affected knee OA symptoms, time with knee OA symptoms, consultation with an orthopaedic surgeon in the past, appointment to see an orthopaedic surgeon arranged, previous surgery, previous injury to the affected knee, and presence of contralateral TKA. The baseline questionnaire will also capture the VR-12 and the Euroqol 5 Dimensions 3 Levels (EQ-5D-3L) data to understand the baseline HRQoL utility score for each group.

For participants in the intervention group, the study portal will allow access to the *SMART Choice* tool and provide a predicted outcome for the participant. Inputs onto the tool will be captured electronically; however, the participant will have the option to download a copy of their results for personal reference. Participants in the TAU group will not have access to the *SMART Choice* tool or predicted outcome and will instead continue with the regular assessments for the remainder of the study.

Following the baseline questionnaire (or *SMART Choice* tool use for the intervention group), participants will be asked to complete regular assessments in accordance with the Schedule of Assessments (Tables 2 and 3). This will consist of “willingness for surgery”, “already proceeded with surgery”, and decision quality questionnaires.

**Table 3 Tab3:** Definitions for SoA

Terms	Definitions	
Time Point	***t***_***x***_	Time at initial contact via email with PIS, CF, and eligibiility screen. If a patient is eligible and consents, allocation will immediately follow this time.
	**t**_**0**_	Time at allocation with initial concurrent assessments.
	***t***_***1***_	Immediately after allocation, for prognostic tool use in TAU group.
	***t***_***2***_	6 weeks after initial assessment (t_0_)

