	***t***_***3***_	12 weeks after initial assessment (t_0_)
	***t***_***4***_	6 months after initial assessment (t_0_)
	***t***_***y***_	Time at study closure for individual participant. This should be equal to t_4_ if all assessments are completed on schedule.
Baseline Questionnaire	Questionnaire for all patients who have been allocated in the study. Same for all groups. Captures basic demographic data as well as questions about previous knee treatment and surgery. This section will also capture baseline health-related quality of life through the VR-12 and EQ-5D-3L.	
Wilingness for Surgery	This assessment asks the question "Are your knee symptoms so bothersome that you wish to undergo surgery if medically fit to do so?" Yes / No. If yes, "In what time frame are you willing to have surgery?" [Time in months].	
Already Proceeded with Surgery	This assessment asks the question "Have you already received a TKA for your knee symptoms?" Yes / No. The purpose for this assessment is to 1) check if the patient has undergone TKA, and 2) outcome aligns with their willingness for surgery response.	
Qualitative Questionnaires	This assessment consists of K-DQI (decision quality) and SURE (decisional conflict) tools.	

*PIS* participant information sheet, CF consent form, *TKA* total knee arthroplasty, *OA* osteoarthritis, *VR-12* Veterans-RAND 12, *EQ-5D-3L* EuroQol 5 Dimensions 3 Levels, *K-DQI* Knee Decision Quality Instrument, *SURE* decisional conflict screening tool

The initial assessment will be the first timepoint at which regular assessments will be performed. At the end of the initial assessment, participants will be thanked for their time and be reminded of follow-up. Participants will receive emails with access to the study portal at subsequent follow-up periods: 6 weeks, 3 months, and 6 months after recruitment.

Willingness for surgery assessment consists of a single binary question: “Are your knee symptoms so bothersome that you would be willing to undergo surgery if medically fit to do so? (Yes/No)” If yes, “In what time frame are you willing to have surgery?” [Time in months]. The purpose of this assessment is to evaluate whether the patient is still of the mindset to proceed with surgery.

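### The trial is labelled assessor-blinded, but its primary outcome is reported by unblinded participants and no outcome has an independent assessor

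*Protocol article*

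**What the plan says.** All of the relevant text is in the Methods of the protocol article.

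- **Design label** (Study design and setting): "This is a prospective, pragmatic, assessor-blinded, superiority randomised controlled trial".
- **Participants** (Randomisation, allocation, and blinding): "Due to the nature of the study, participants will remain unblinded from their allocation group".
- **Investigators** (same section): "Investigators (excluding research assistants who will not be involved in data analysis) will remain blinded to the allocation group and identity of patients", until the final analysis has been done.
- **Surgeons** (same section): "Surgeons will be blinded to the allocation group of their patients".
- **Primary outcome** (Outcomes; Participant timeline and assessments): "Willingness for surgery assessment consists of a single binary question", put to the patient and answered yes or no.
- **Mode of collection** (Data collection and management): the participant completes the regular assessments in the online portal under their own credentials. A mailed paper version exists for those who need it, and a research assistant enters those data.

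**The concern.** Assessor-blinded tells a reader that whoever determined the outcome did not know the allocation. For a self-reported outcome, the person who determines it is the participant, and here the participant knows the allocation. The label and the blinding section cannot both hold for the primary outcome.

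Willingness to have surgery is a subjective answer. In the intervention arm it comes from someone who knows that they used a prediction tool. A difference between arms may therefore mix a real change of mind with a change in how the question is answered. The label suggests that the second part has been controlled. A reader or a later evidence synthesis that relied on it would rate the protection against measurement bias too favourably.

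**Working it through.** No figure is attached to the blinding claim, so the check sets text against text.

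**1. Who rates each outcome?**
- Willingness for surgery: the participant (Outcomes; Table 3).
- Whether TKA has already been received: the participant, by a yes/no question (Table 3).
- K-DQI and SURE: the participant, by questionnaire (Participant timeline and assessments).

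The mailed route changes the medium, not the rater.

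**2. Who is blinded?** Investigators and surgeons. Participants are not, and research assistants are excepted.

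**3. Overlap.** Raters = {participants}. Blinded = {investigators, surgeons}. The two sets have no member in common, so no outcome has a blinded assessor.

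**4. Does anything else supply the missing protection?**
- Limited disclosure does not. Its stated purpose is different: "limited disclosure of allocation groups will be applied to prevent participants who are allocated to TAU from proactively seeking out online prognostic tools to use". It may leave some TAU participants unsure what the other arm received, but intervention participants know that they used the tool.
- Research assistants do not. They are the staff nearest to outcome collection, since they support completion of assessments (Statistical plan) and enter paper data, but they are the role exempted from blinding.

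**5. Is it acknowledged as a limitation?** The Discussion lists missing surgical and clinical predictors, use of other online tools, and the technology barrier for older participants. It does not mention an unblinded self-reported primary outcome.

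**6. Can the bias be given a size or a direction?** The documents give no figure for it. Table 1, which the article presents as an example, suggests that even the sign is open:
- Predicted improvement: 63 + 5 × 68 = 403.
- Predicted deterioration or no change: 4 × 69 + 5 = 281.
- Total: 684, so 403/684 = 59% and 281/684 = 41%.

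If participants tended to answer in line with their prediction, some would be pushed towards yes and others towards no.

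**7. Is the sample size involved?** No. For 65% against 50%, two-sided 5% and 80% power, the pooled formula gives 170 per arm and the arcsine formula 169.1. The stated 169 reproduces, and the point does not depend on it.

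**8. How many TKA events could 6 months yield?** SVHM participants are identified from clinic lists up to 3 months ahead. After consultation they may wait another 6 to 12 months for surgery. With those waits, even a participant seen on the day of enrolment would reach surgery at about 6 months at the earliest, which is the end of follow-up. HCF participants are at varied stages, and some have already applied for TKA funding. The Background itself says that waiting for actual TKA would not be feasible.

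**The case against.** The strongest reply is that the article hides nothing. Its blinding section says plainly that participants are unblinded and lists who is blinded and who is not. Unblinding cannot be avoided, because receiving the prediction is the intervention and responding to it is the intended effect. Correcting the label changes no estimand, test or sample size. All of this stands, and it limits the point to a label and an unstated limitation. It does not make the label right: blinded analysts protect the analysis, not the measurement.

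A reader might infer more than the documents support:

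- **That surgeon blinding is also false**, because "the participant will have the option to download a copy of their results for personal reference". Nothing says that participants take the result to a consultation. Possible later disclosure by a patient does not contradict blinding as a study procedure, and surgeons rate no outcome.
- **That every outcome is biased to the same degree.** Receipt of TKA is a matter of fact and less open to response bias. The text sends K-DQI and SURE to the intervention group only, which leaves no comparison between arms to bias, although Table 2 marks both groups.
- **That participants answer straight after seeing the prediction.** Table 2 schedules no willingness question at the time of tool use; the next ones are at 6 weeks, 12 weeks and 6 months. The text is unclear about how the initial assessment is ordered relative to tool use.
- **That the bias is some stated share of the planned 15-point difference.** Any such share would rest on an assumed shift in an assumed direction.

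**Conclusion.** The point holds as a mislabelled design property. The label claims blinded outcome assessment, whereas the primary outcome is self-reported by participants whom the article calls unblinded, and no outcome has an independent rater. The blinding of investigators and surgeons is worth stating, but it is a different protection.

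The numerical consequence cannot be derived: the response bias in willingness has unknown size and direction. The practical consequence is for interpretation, namely how far a difference in stated willingness can be read as a change in decision. The conclusion rests only on reading assessor in its usual sense, the person whose judgement or answer fixes the outcome value.

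**What to change.** - In Study design and setting, replace the term assessor-blinded with wording such as: *open-label for participants, with participant-reported outcomes and blinded investigators/data analysts*. The blinding section can stay as it is.
- Add one sentence to the limitations: the willingness result comes from unblinded participants and is open to response bias of unknown size and direction.
- Report receipt of TKA by 6 months by arm as a supportive, more factual outcome. It is already collected at 6 weeks, 12 weeks and 6 months. State beside it that it is also self-reported and that events may be few given the waiting times described.

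The cost is one changed label, one added sentence and one table from data already collected. The stated design will look slightly less favourable.

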### Intervention and comparison groups

Participants in the intervention group will receive use of the *SMART Choice* tool at the beginning of the study, as outlined in Table 1. The tool uses patient-focused parameters, including age, sex, body mass index (BMI) and VR-12 survey, to predict the likelihood of improvement after TKA. The predicted outcome is displayed in a format that is similar to the *After My Surgery* tool from the University of York [28]. This format uses a patient-friendly output of how 100 patients who were similar to the user felt after TKA surgery (Fig. 1). All other aspects of the study for participants in the intervention group will be identical to the TAU group.

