**ASSESSMENTS:**							
**Baseline questionnaire**		X					
**Willingness for surgery**		X		X	X	X	X
**Already proceeded with surgery**				X	X	X	X
**Qualitative questionnaires **						X	X

See also Table 3 for definitions and timepoints. I = intervention group. TAU = treatment as usual group. X = participants in both intervention and treatment as usual groups

The secondary outcomes for this study include:Determining the optimal timepoint for prognostic tool use in a patient’s TKA journey to maximise the effect on willingness to undergo surgery.Determine whether there are differences in the effectiveness of the *SMART Choice* tool when used in subpopulations such as sex, gender, and ethnicity.Understanding the user experience and effect on decision making of the *SMART Choice* tool through decision quality questionnaires.

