**Table 4 Tab4:**

Binary items used in the SURE screening tool to assess decisional conflict

If a patient answers “no” to 1 or more questions, then the screen is considered positive for decisional conflict. Understanding decisional conflict is important to ensure that the information provided by *SMART Choice* is presented with clarity and aids the overall experience for patients on their TKA journey.

All participants will have free access to the *SMART Choice* tool at the completion of the study period.

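### The journey-stage sub-analysis can show whether the tool's effect differs by stage at enrolment; it cannot identify an optimal time to use the tool

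*Protocol article*

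**What the plan says.** **Objective.** The first secondary outcome (Protocol article, Outcomes) begins "Determining the optimal timepoint for prognostic tool use" and adds that the aim is to maximise the effect on willingness for surgery. The Abstract's hypothesis expects more influence when the tool is used earlier. Study design and setting says that the optimal timepoint "will be evaluated from a sub analysis of patients at different timepoints in the TKA journey". The Statistical plan adds only that each participant's position on the journey will be recorded and used.

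**Timing of use.** Under Intervention and comparison groups, the intervention arm receives the "tool at the beginning of the study". Table 2 marks tool use at one visit, t1, for the intervention group only. TAU participants get access to the "tool at the completion of the study period" (Participant timeline and assessments). Table 3 attaches tool use at t1 to the TAU group. Table 2, the intervention section and the Statistical plan all contradict that entry, so I read it as a slip.

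**What is randomised.** Tool versus TAU, 1:1, by simple randomisation. Neither stage nor source is named as a factor.

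**How stage arises.** At SVHM, "patients who have been referred to an orthopaedic surgeon for consideration for TKA will be targeted for recruitment", and the protocol says these patients are often late in the journey. HCF members range from very early disease to having already applied for surgical funding. The plan is 200 from each source.

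**The concern.** Naming a best time to offer the tool is a causal statement about timing: the same kind of patient, given the tool earlier, would respond differently. The trial contains no such contrast. It compares the tool's effect in people who entered at an early stage with its effect in people who entered at a late stage, and these groups differ in more than stage.

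If the effect on willingness proves larger in early-stage participants, the objective as worded leads directly to a recommendation to deliver the tool earlier. The same result could arise because early-stage participants come more from a private insurer, face a different usual-care comparator, or have milder disease. The limitations in the Discussion do not say that stage is non-randomised.

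**Working it through.** **1. What the design identifies.** Set side by side:

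| Element | Where stated | Varies by randomisation? |
|---|---|---|
| Tool versus TAU | Randomisation, allocation, and blinding | Yes |
| Time of tool use within the study | Intervention section; Table 2 | No, fixed at entry |
| Journey stage at entry | Study design and setting | No, a recruited characteristic |

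The effect of tool versus TAU within early-stage participants, and the effect within late-stage participants, are each randomised comparisons. Their difference is a valid estimate of effect modification by stage. Attributing that difference to timing would require stage to be unrelated to other modifiers of the effect.

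**2. What the protocol ties to stage.**
- Source: SVHM often late, HCF mixed (Study design and setting).
- Comparator: TAU is said to differ between institutions (Intervention and comparison groups).
- Severity and willingness: earlier stage is described as less severe, with lower expected baseline willingness (Sample size and recruitment).

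**3. The plan's own figure.** The stated size is 169 per arm for 65% versus 50%, two-sided 5%, 80% power. The arcsine formula gives 2 × (2.80 / 0.3047)² = 169.1. Pooled and unpooled normal formulas give 170 and 167. The figure reproduces, but it covers only the overall comparison. No figure is given for the stage analysis.

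**4. Precision of the stage contrast.** Inputs from the protocol are 200 per arm, 200 participants per source, and 65% versus 50%. My assumptions are two stages of equal size, the same two rates in each stage for the variance, a normal approximation and full follow-up.

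- Variance of one risk difference with n per arm: (0.65 × 0.35 + 0.50 × 0.50) / n = 0.4775 / n.
- SE of the difference between two such effects: √(2 × 0.4775 / n).
- Detectable difference at 80% power: (1.96 + 0.84) × SE = 2.80 × SE.

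| Contrast | n per arm per stage | SE | Detectable difference |
|---|---|---|---|
| Whole trial | 100 | 0.0977 | 27.4 points |
| HCF only (200 people, 100 per arm) | 50 | 0.1382 | 38.7 points |

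For a true 15-point effect in early-stage and none in late-stage participants, the whole-trial SE is √[(0.2275 + 0.25 + 0.2275 + 0.2275) / 100] = 0.0966. Power is Φ(0.15 / 0.0966 − 1.96) = Φ(−0.41), about 34%.

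**5. Effect of unequal stages.** If all SVHM participants were late and HCF split evenly, the trial would have 100 early and 300 late participants. The unadjusted SE would be √(0.4775/50 + 0.4775/150) = 0.1128, so 2.80 × 0.1128 gives about 32 points. With arm-by-source in the model, the stage contrast would then come from HCF alone, at about 39 points. The protocol says only that SVHM patients are often late, so this is a limiting case.

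**The case against.** The best defence is that the protocol means time along the patient's journey, not time within the study. On that scale timing does vary between participants, by deliberate recruitment at all stages, and tool versus TAU is randomised within each stage. For the practical question of which patients to offer the tool to, stage-specific effects are useful. The hypothesis under Study design and setting is also hedged, and model terms are properly left to an analysis plan that is not shown. Most of this stands. It supports keeping the analysis, and the absence of interaction terms from the article is not itself a fault. It does not support the stated conclusion, since no model in an unseen plan turns recruited stage into a randomised timing contrast.

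Stronger readings are tempting and should be resisted:

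- *The stage-specific effects are themselves confounded.* They are not; only the explanation of their difference is open.
- *Stage is simply source.* HCF spans the whole range, and baseline items on symptom duration and orthopaedic consultation or appointment help describe stage within each source.
- *Early users will be shown poorer predictions, which alone will create a stage difference.* The tool uses VR-12 and early disease is called less severe, so a link is conceivable. But nothing in the document relates stage or baseline VR-12 to the prediction shown, Table 1 is labelled an example, and the model is not final. Direction and size cannot be derived. If early users do see different predictions, that may be part of what early use does, and so a pathway rather than a confounder.
- *The trial is underpowered.* It is sized for its primary outcome, and low interaction power is ordinary for a secondary analysis. It matters here only for how firmly the result may be worded.

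**Conclusion.** The point holds as a mismatch between a stated objective and the design. The sub-analysis can estimate whether the tool's effect on willingness differs by journey stage at enrolment. It cannot establish an optimal timepoint, because timing was not allocated and stage is partly tied, in the protocol's own account, to source, usual care and severity. The primary comparison is unaffected.

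The size of any bias in a timing interpretation cannot be computed from the document, and I give none. The precision figures, about 27 points overall and 39 within HCF, rest on equal stage splits, 65% versus 50% willingness in both stages and complete follow-up; losses would widen them. Both exceed the 15 points for which the whole trial is sized, so a null stage result would say little and a positive one would remain open to several explanations.

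**What to change.** 1. Restate the first secondary outcome, and the part of the hypothesis about earlier use, as effect modification by journey stage at enrolment. Drop the optimal timepoint as a conclusion in the Abstract, Background, Study design and setting, Outcomes and Statistical plan, and add to the limitations that stage is not randomised.
2. Estimate it with an arm-by-stage interaction in a model that also contains arm-by-source, with the corresponding main effects.
3. Report the stage contrast within HCF separately, as the source described as covering a range of stages.
4. Label the analysis exploratory and report interaction estimates with confidence intervals.
5. Optionally, add arm-by-predicted-score as a sensitivity analysis only. The score can be computed in both arms from baseline date of birth, sex, height, weight and VR-12. It should not be the main analysis, because conditioning on the prediction may remove a genuine consequence of early use.

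The cost is wording, one further interaction with its main effect, and, if item 5 is taken up, background scoring of TAU baseline data. Recruitment, visits and the intervention do not change. The downside is a weaker claim and a wider interval for the stage effect. A true timing claim would need the time of access to be randomised, which is a different trial.
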